### 7.1. Defining, Grading and Recording of AEs

#### 7.1.1. Definition of an AE & Serious Adverse Event (SAE)

An **AE** is defined as any untoward medical occurrence in a patient or clinical investigation participant undergoing a medical intervention and which does not necessarily have a causal relationship with the treatment. An AE can therefore be any unfavorable and unintended sign (including an abnormal laboratory finding, for example), symptom, or disease temporally associated with the medical intervention, whether or not it is considered related to the medical intervention. For purposes of this study, AEs will be defined as a change from the patient's baseline that occurs in temporal relationship to any study related procedures (i.e. insertion of the intrathecal catheter or drainage of CSF).

An **SAE** is defined as any untoward medical occurrence that:

- results in death,
- is life-threatening,

*Note: the term "life-threatening" refers to an event in which the patient was at risk of death at the time of the event; it does not refer to an event which hypothetically might have caused death if it were more severe.*

- requires inpatient hospitalization or prolongation of existing hospitalization,
- results in persistent or significant disability/incapacity,
- is a congenital anomaly/birth defect,

- is a medically important event or reaction that may not be immediately life-threatening or result in death or hospitalization, but may jeopardize the patient or may require intervention to prevent one of the other outcomes listed above.

Medical and scientific judgment should be exercised in deciding whether expedited reporting is appropriate in other situations, such as important medical events that may not be immediately life-threatening or result in death or hospitalization but may jeopardize the patient, or may require intervention to prevent one of the other outcomes listed in the definition above.

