### 3. RESEARCH OBJECTIVES

**Objective 1.** To determine if actively maintaining an SCPP of at least 65 mmHg with a combination of MAP augmentation and CSF drainage promotes better neurologic recovery than routine hemodynamic management that focuses solely on MAP augmentation.

We will compare the neurologic recovery in our patients who receive active SCPP management against our prospectively collected CAMPER cohort, a cohort who had intrathecal catheters placed but only routine MAP management. Active SCPP management will be achieved clinically by a combination of MAP augmentation and CSF drainage to lower ITP.

**Objective 2.** To determine if actively maintaining an SCPP of at least 65 mmHg with a combination of MAP augmentation and CSF drainage will allow for a reduction in the usage of vasopressors in acute SCI.

Data that has emerged from UCSF has really highlighted the potential adverse events (AEs), such as arrhythmias and troponin elevations, related to MAP augmentation with vasopressors [21, 22]. We have also witnessed cardiac ischemia in elderly individuals where vasopressors were aggressively used to augment MAP. In many past cases, we have felt that the acute SCI patient has required extremely high doses of vasopressors to achieve a standard MAP target, and that this could be quite deleterious. So, there definitely is an underlying rationale for determining whether a different approach (one that involves both MAP augmentation and CSF drainage) can reduce vasopressor requirements.

We will be tracking MAP, ITP, and SCPP, and the concomitant vasopressors required to maintain an SCPP of  $\geq 65$  mmHg. We will be able to compare this with vasopressor usage in our past CAMPER patient cohort to determine if this approach can allow for a reduction in vasopressor usage.

**Objective 3.** To determine the feasibility of draining CSF to reduce ITP in the acute post-injury setting, when the cord may be swollen against the dura causing subarachnoid space occlusion at the injury site.

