**Objective 4.** To determine if there are complications associated with the installation of the intrathecal catheter and drainage of CSF in the acute SCI patient.

It goes without saying that we will measure AEs associated with intrathecal catheter placement. Of course, acute SCI patients incur a huge number of AEs; but we have utilized a system of daily monitoring those that are most applicable to the lumbar catheters – namely CSF leak/postural headache, nausea/vomiting, and infection. The patients will be carefully monitored by the study research team throughout the time that they have the intrathecal catheter placed.

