#### **MAP MANAGEMENT**

MAP will be monitored with an arterial line. The focus in the CASPER trial will be on the SCPP, but MAP augmentation, when needed, will be achieved with volume replacement (i.e. crystalloid, colloid, or whole blood) followed by vasopressors as needed. At Vancouver General Hospital, norepinephrine is the vasopressor of choice, based on locally conducted animal and clinical studies [25, 26]. It is recognized however, that other sites may use different vasopressors based on clinical preference/familiarity and that strong clinical evidence to support one vasopressor over another is not available.

***What will the MAP target be?*** Patients should not be allowed to be HYPOTENSIVE and thus, MAP augmentation should be instituted if their systolic BP is less than 90 mmHg. Based on the clinical practice of the specific institution, if the ICU staff wish to maintain MAP at 85 mmHg, this would be accepted. But we will not mandate a target MAP of 85 mmHg.

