#### **7.2. Relationship Between AEs and CSF Drainage or Insertion, Presence, or Withdrawal of the Lumbar Intrathecal Catheter**

The relationship between AEs and the insertion and presence of the lumbar intrathecal catheter will be defined as follows:

**Probable:** A clinical event including, laboratory test abnormality, with a reasonable time sequence to insertion and presence of the lumbar intrathecal catheter unlikely to be attributed to concurrent disease or other drugs or chemicals and which follows a clinically reasonable response on withdrawal (dechallenge). Rechallenge information is not required to fulfill this definition.

**Possible:** A clinical event, including laboratory test abnormality, with a reasonable time sequence to insertion and presence of the lumbar intrathecal catheter but which could also be explained by concurrent disease or other drugs or chemicals. Information on Intrathecal catheter removal may be unavailable or unclear.

**Unlikely:** A clinical event, including laboratory test abnormality, with temporal relationship to insertion and presence of the lumbar intrathecal catheter which makes a causal relationship improbable and in which other drugs, chemicals or underlying disease provide plausible explanations.

**Unrelated:** The clinical event can in no way be related to the insertion or presence of the intrathecal catheter.

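### The tested strategy includes vasopressor-supported MAP augmentation, whose cardiac harms the protocol names, but adverse events are defined, rated and reviewed only against the catheter or CSF drainage

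*Protocol*

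**What the plan says.** Objective 1 (Protocol, Section 3) asks whether "actively maintaining an SCPP of at least 65 mmHg with a combination of MAP augmentation and CSF drainage promotes better neurologic recovery" than management aimed at MAP alone. Under MAP Management in Section 5.3, MAP is raised by volume replacement "followed by vasopressors as needed".

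Objective 2 asks whether the strategy reduces vasopressor use. Its rationale is safety. It cites "potential adverse events (AEs), such as arrhythmias and troponin elevations, related to MAP augmentation with vasopressors" and adds: "We have also witnessed cardiac ischemia in elderly individuals where vasopressors were aggressively used to augment MAP".

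The safety text is narrower:

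- Section 7.1.1 first gives a general adverse event definition that does not depend on relatedness. For this study it then limits adverse events to changes from baseline "in temporal relationship to any study related procedures (i.e. insertion of the intrathecal catheter or drainage of CSF".
- Objective 4 concerns complications of catheter placement and drainage. Its daily monitoring is directed at the events "most applicable to the lumbar catheters – namely CSF leak/postural headache, nausea/vomiting, and infection".
- Section 7.1.3 calls for recording every adverse event in the reporting window, which opens at insertion and closes a day after the catheter comes out. Its directed questions concern catheter side effects, and its relationship field concerns the catheter or drainage.
- Section 7.1.4 requires every serious adverse event to go to the project manager and the site's ethics board.
- Section 7.2 words each causality category against the catheter. The lowest reads: "The clinical event can in no way be related to the insertion or presence of the intrathecal catheter".
- The introduction to Section 7 has the board review complications of catheter insertion and presence, after 10 and after 50 patients.

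**The concern.** The protocol treats MAP augmentation as part of the intervention when it states what is tested, and as a source of harm when it justifies Objective 2. It then leaves that component out of the machinery that decides what counts as a study adverse event, what it is judged against and who sees it.

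Two things are at stake. The first is the safety statement on active SCPP management: a conclusion drawn from the relationship ratings and the board's review would describe the catheter, and in part the drainage, but not the whole strategy. The second is Objective 2. Lower vasopressor use matters because of the harm it may avoid, but the stated comparison with CAMPER stops at usage.

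**Working it through.** No sample size, power or error-rate figure bears on this point, and the protocol states no rate of cardiac events. The check is a comparison of text.

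**Step 1. Components of the strategy.** Objective 1 and Section 5.3 give two: MAP augmentation (volume, then vasopressors) and CSF drainage through the catheter.

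**Step 2. What each safety element covers.**

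| Safety element | Place | Catheter | Drainage | MAP augmentation |
|---|---|---|---|---|
| Study-specific AE definition | 7.1.1 | yes | yes | no |
| Safety objective | Objective 4 | yes | yes | no |
| Directed inquiry | 7.1.3 | yes | no | no |
| Relationship field | 7.1.3 | yes | yes | no |
| Causality categories | 7.2, body | yes | no (section title only) | no |
| Local investigator sign-off | 7, introduction | yes | no | no |
| Board remit | 7, introduction | yes | no | no |

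Count: catheter 7 of 7, drainage 3 of 7, MAP augmentation 0 of 7. The complications described in Section 7.3 include no cardiac event either.

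**Step 3. Follow one event through the plan.** Take a new arrhythmia in a patient on a vasopressor while the catheter is in place.

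- *Recording.* The all-events rule in 7.1.3 captures it. The narrowed definition in 7.1.1 is less clear, because it ties timing to insertion or drainage and introduces these two with *i.e.*, which closes the list. The general definition just before it would include the event. The two definitions and the recording rule therefore do not set one boundary.
- *Rating.* *Probable* requires that other drugs be an unlikely cause, which fits poorly. *Possible* allows that another drug could explain the event. *Unlikely* applies when the timing makes a link to the catheter improbable and other drugs are plausible explanations. *Unrelated* needs the link to be ruled out. So *possible*, *unlikely* or *unrelated* could each be chosen, and each would state a relation to the catheter. None would state a relation to MAP augmentation.
- *Escalation.* If serious, it goes to the project manager and the ethics board under 7.1.4. The protocol states no route from there to the safety board, whose remit is catheter complications.
- *Reporting.* Objective 2 tracks vasopressors alongside MAP, ITP and SCPP, and compares usage with CAMPER. It states no link between that exposure and the event.

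**Step 4. Result.** The event can be recorded and, if serious, reported. The plan provides no rating of it against the component the protocol itself identifies as its likely cause, and no board review of it.

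**The case against.** The strongest reply has three parts.

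First, nothing is lost. All adverse events in the window are recorded with dates, severity and concomitant treatment, all serious events are reported whatever their cause, and vasopressor use is tracked. This stands in part. A reader might infer that cardiac events go unrecorded, that sites are compelled to call them unlikely or unrelated, or that they can never be attributed. The documents support none of these: Sections 7.1.3 and 7.1.4 capture the events, Section 7.2 leaves *possible* open, and event records could later be linked to vasopressor data. But recording is not rating, no such linkage is stated, and a relationship never collected cannot be restored by an analysis plan.

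Second, vasopressor support is background care. CAMPER patients had routine MAP management, CASPER mandates no MAP target of 85 mmHg, vasopressor use follows site practice, and drainage is meant to spare vasopressors. It is fair that MAP augmentation is not unique to CASPER. As a reason for leaving it out it fails, because the catheter is also placed by clinical decision and its complications are still rated and reviewed. Objective 2 also makes vasopressor exposure a study question.

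Third, acute SCI patients have very many adverse events, so a narrow focus is practical. That is a sound reason not to solicit everything. It does not explain omitting the few harms that Objective 2 names.

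A reader might also infer that exposure rises sharply when drainage fails, by combining SCPP = MAP − ITP with the postoperative peak pressures in Section 2.3 and the swelling figure under Objective 3. The documents do not support this. The pressures are peaks from a 24-patient trial, the swelling figure describes imaging after decompression rather than failed drainage, and the management algorithm (Figure 16) is not visible in the text available.

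**Conclusion.** The point holds as a gap in attribution and oversight, not in recording. As written, a vasopressor-related event in the catheter window is judged only against the catheter or drainage, falls outside the board's stated remit, and is not set beside the vasopressor comparison in Objective 2. The causality categories and the board remit omit even CSF drainage, which is the component CASPER adds.

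Its size is the text count: none of the seven safety elements mentions MAP augmentation. No number of affected patients can be given, because the protocol states no rate of cardiac events under vasopressors. The primary efficacy comparison is not affected.

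The conclusion assumes that the relationship categories and board remit are applied as printed. A board charter or case report form that already covers every component would remove much of the concern, and the protocol should then say so.

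**What to change.** 1. **Section 7.1.1:** reconcile the study-specific definition with the general definition before it and with the all-events rule in Section 7.1.3, so that one boundary applies.
2. **Sections 7.1.3 and 7.2:** rate relationship separately to the catheter, to CSF drainage, and to MAP augmentation (fluids or vasopressors) given to maintain SCPP. Extend the directed inquiry to the cardiac events named under Objective 2.
3. **Section 7, introduction:** widen the board remit to events related to any component of the strategy, including drainage.
4. **Objective 2:** report clinically documented arrhythmia, troponin elevation and myocardial ischemia in CASPER patients beside their vasopressor exposure. The protocol does not say whether CAMPER holds comparable cardiac data, so a comparison between cohorts should be promised only if it does. The detail of the tables can sit in the analysis plan.

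No new test and no change to clinical management is needed. The cost is protocol and case report form wording, more adverse event entries, and transcription of events already in the clinical record. Ascertainment would be limited to tests ordered for clinical reasons, so troponin elevation in particular would reflect local testing practice and should be reported with that caveat.

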### 7.1.2. AE Grading

Severity of AEs will be graded according to the National Institute of Health Common Terminology Criteria for Adverse Events (CTCAE), Version 4.0, using the following definitions:

#### Grades

Grade refers to the severity of the AE. The CTCAE displays Grades 1 through 5 with unique clinical descriptions of severity for each AE based on this general guideline:

- Grade 1 (Mild); asymptomatic or mild symptoms; clinical or diagnostic observations only; intervention not indicated.
- Grade 2 (Moderate); minimal, local or non-invasive intervention indicated; limiting age-appropriate instrumental activities of daily living (ADL).
- Grade 3 (Severe or medically significant but not immediately life-threatening); hospitalization or prolongation of hospitalization indicated; disabling; limiting self-care ADL.
- Grade 4 (Life-threatening consequences); urgent intervention indicated.
- Grade 5; Death related to AE.

### 7.1.3. Recording of AEs

All AEs that occur during the reporting period, insertion of catheter to 24 hours post-removal, will be recorded in the Adverse Event case report forms. AE data will be obtained from any information volunteered by the patient or through patient questioning. Both the passive system of recording AEs and directed inquiry regarding known potential side effects of insertion and presence of the lumbar intrathecal catheter (see below) will be utilized. Additional information to be recorded includes the **duration** of the AE (onset/resolution dates), **severity**, **relationship** to the insertion and presence of the lumbar intrathecal catheter or drainage of CSF (classified as “probable”, “possible”, “unlikely” or “unrelated” - see below) and any **concomitant treatment** dispensed (or other action taken). All “serious” and “unexpected” AEs will be reported to the local REB as per local institutional guidelines. Additionally, the ‘Serious and Unexpected’ Adverse Events will be reported to the CASPER Project Manager.

#### **7.1.4. SAE Reporting**

All SAEs that occur during the course of the study must be reported to the CASPER Study Project Manager by telephone within 24 hours of the site becoming aware of the event. When appropriate, the SAE will be documented on the “Serious and Unexpected Adverse Event” case report form and submitted to the CASPER Study Project Manager within 48 hours. All SAEs must be reported to the site’s REB according to the local requirements.

#### **7.2. Relationship Between AEs and CSF Drainage or Insertion, Presence, or Withdrawal of the Lumbar Intrathecal Catheter**

The relationship between AEs and the insertion and presence of the lumbar intrathecal catheter will be defined as follows:

**Probable:** A clinical event including, laboratory test abnormality, with a reasonable time sequence to insertion and presence of the lumbar intrathecal catheter unlikely to be attributed to concurrent disease or other drugs or chemicals and which follows a clinically reasonable response on withdrawal (dechallenge). Rechallenge information is not required to fulfill this definition.

**Possible:** A clinical event, including laboratory test abnormality, with a reasonable time sequence to insertion and presence of the lumbar intrathecal catheter but which could also be explained by concurrent disease or other drugs or chemicals. Information on Intrathecal catheter removal may be unavailable or unclear.

**Unlikely:** A clinical event, including laboratory test abnormality, with temporal relationship to insertion and presence of the lumbar intrathecal catheter which makes a causal relationship improbable and in which other drugs, chemicals or underlying disease provide plausible explanations.

**Unrelated:** The clinical event can in no way be related to the insertion or presence of the intrathecal catheter.

#### **7.3. Complications Associated with Lumbar Intrathecal Catheter Insertion or CSF Drainage**

As the intrathecal catheter is being inserted as part of the clinical hemodynamic management of the patient, the management of AEs will be left to the discretion of the treating physician. The nature of the AE and the decisions made by the treating physicians will be documented. Below is a description of known complications associated with lumbar catheter insertions and CSF drainage, with estimated incidences.

### 7.3.1. Post-dural Puncture Headache

The most common risk after lumbar intrathecal catheter insertion is the development of a post-dural puncture headache (PDPH), which may be associated with nausea and vomiting. The incidence of these symptoms has been variably described to be between 2.5% [30] to 59% [31]. ***Because acute SCI patients are not being mobilized into an upright position right away, we expect the risk of this complication to be low in the study population. In the CAMPER study, there were no cases of post-dural puncture headache.***

### 7.3.2. Neurologic Injury from Lumbar Intrathecal Catheter Insertion or CSF drainage

The placement of the needle (typically a 14-gauge malleable needle) into the lumbar intrathecal space and the insertion of the catheter itself has the potential to injure lumbosacral nerve roots. Grady and colleagues reported on 513 patients in whom CSF drainage was performed while the patient was anesthetized; they found no neurologic deficits [30]. Auroy et al. found 24 cases of neurologic injury in a prospective analysis of 40,640 spinal anesthetics (0.06%) [32]. In a retrospective review of 1.26 million spinal blocks done in Sweden over a decade (1990-1999), Moen et al. identified 56 complications (0.004%) [33]. ***In an extensive review of neurologic complications performed in 2015, ASRA summarized the risk of neuraxial injury to range from 0.001% to 0.07% [34].***

### 7.3.3. Thromboembolic Prophylaxis for Intrathecal Catheter Insertion and Removal

Patients with complete paralysis are at increased risk of thromboembolic disease. The most recent (2017) clinical practice guidelines from AOSpine recommend the use of low molecular weight heparin (LMWH) to reduce the incidence of thromboembolic disease in SCI patients [35]. The LMWH that will be used for this study is enoxaparin which is administered subcutaneously once daily (40 mg).

Inserting a needle and intrathecal catheter into the epidural space engenders a small risk of epidural hematoma, which is expectedly increased when the patient is anticoagulated. This has therefore incited a number of studies to evaluate the safety of regional spinal anesthesia in the setting of pharmacologic anticoagulation. Practice guidelines have therefore been established based on numerous studies that have documented the safety of regional anesthesia techniques in the patient receiving thromboembolic prophylaxis. The most recent (2018) guidelines set by ASRA and Pain Medicine ASRA specifically address the usage of once daily and twice daily LMWH [28]. The guidelines generally reflect the fact that the increased risk to the patient occurs when the intrathecal catheter is physically either inserted or when it is withdrawn/removed (i.e., when there is a sudden distortion of the epidural space). For this reason, the following has been recommended:

For patients in whom LMWH has begun prior to the insertion of the intrathecal catheter, the guidelines recommend “delay of at least 24 hours prior to needle/catheter placement”. Because the lumbar intrathecal catheter is placed within 24 hours of injury, it would be extremely unusual

for a patient to arrive at a specialized trauma centre already on thromboembolic prophylaxis, and thus, we anticipate that this scenario of having to consider patient's coagulation status prior to lumbar intrathecal catheter insertion will occur only very rarely.

The lumbar intrathecal catheter will be placed prior to the surgical procedure for spinal stabilization. The first dose of LMWH will be administered no earlier than 24 hours post-operatively. The ASRA 2018 guidelines recommend that "the catheter should be removed 12 hours after the last dose of LMWH. Subsequent LMWH dosing should occur at least 4 hours after catheter removal" [28].

